We will conduct a 10-week, multi-method, randomized study, and will recruit 200 school-based adolescents, ages 12-18 years, with daily or near daily cannabis use and current depressive symptoms. The study design is nearly identical to that used in another IRB approved protocol aimed at pilot data collection for the current protocol (#2021P002416), apart from minor modifications to the study population. Participants will complete 2 weeks of real-time EMA during baseline cannabis use (EMA Phase 1; Baseline Use as Usual) to quantify the temporal relationship between cannabis use and mood and SI, and the within- (e.g., concurrent other substance use, social context of use) and between-subject factors (e.g., average severity of cannabis use, depression and SI) that may moderate these linkages. To determine how depression and SI change across short- and longer-term cannabis withdrawal, participants will then be randomized to 8 weeks of monitoring (CB-Mon) or incentivized abstinence via contingency management (CB-Abst). A key aspect of the approach is that the 8-week period is long enough to observe true changes due to cannabis discontinuation, separate from effects of withdrawal and residual cannabinoid exposure that generally subside in 4 weeks. Both groups will complete 1 week of EMA in weeks 1 (EMA Phase 2; Randomized Withdrawal) and 8 (EMA Phase 3; Randomized Sustained Abstinence) of the randomized study period. During all 3 EMA phases, participants will receive 7-9 random, time-stamped prompts per day to ascertain mood and SI in the absence of acute cannabis use, proximal but prior to cannabis use, and during or shortly after cannabis use.

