**Assessment Techniques**

Participants will complete 12 study visits across ~10 weeks and three waves of EMA data collection. To minimize burden and maximize feasibility, study visits will be conducted in a private room at a participant’s school campus or local library, in lab settings, or virtually via video conferencing (via MGB-approved video conference platforms like Microsoft Teams or zoom). Visits will entail collection of urine samples for verification of self-reported use and abstinence verification (for CB-Abst post-randomization), as well as brief questionnaires and interviews on interim substance use, craving, and withdrawal. Questionnaires and surveys on mood symptoms and suicidal ideation (SI) will be conducted by study staff blinded to group assignment.

**Semi-Structured Interviews:** Substance use disorders and other psychiatric diagnoses will be queried at the baseline with past and current modules of the Mini International Neuropsychiatric Interview (MINI) Kid 7.0.2, which was designed as a brief structured diagnostic interview for the major psychiatric disorders across development in DSM-5 (Sheehan, Sheehan, & Shytle et al., 2010). We will evaluate for cannabis use disorder, major depressive disorder, as well as other Axis I diagnoses (including those specific to developmental populations). At the baseline visit, we will administer the Self-Injurious Thoughts and Behaviors Interview (Nock et al., 2007) to assess lifetime self-injurious thoughts and behaviors and confirm past month SI. We will also conduct the Columbia-Suicide Severity Rating Scale (Posner et al., 2011) at V1 to capture in-depth information about past month SI. At V2-12, SI and behavior since last visit will be determined with the Columbia-Suicide Severity Rating Scale *(alongside the primary corresponding EMA measure).* Interviews will be administered by trained study staff with established interrater reliability.

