At the end of 2 weeks, the app will automatically discontinue EMA surveys. Two 1-week EMA phases will occur during the randomized period (weeks 1 and 8 post randomization; Figure 1). Staff will re-train participants on the EMA app prior to each of these EMA phases. Staff members will monitor EMA compliance and will reach out proactively to participants failing to meet criteria. After the third and final EMA phase, participants will be reminded that they will no longer need the EMA app, and that they can delete it (see figure 1 study schema for illustration of EMA administration periods).

All EMA surveys, regardless of phase of the study, will consist of short, multiple-choice items with logic-branched follow-up items. Within each of these surveys, participants will be queried on social settings and activities, cannabis and other substance use, mood, and suicidal ideation. See sections below detailing our plan for data monitoring to ensure safety in the event of SI exacerbation.

**Actigraphy Component (Fitbit): P**articipants will participate in a study component that collects sleep and activity data via a Fitbit Inspire 3. Participants will wear the watch after enrollment at Visit 1 through the Visit 12 (approximately 70 days after enrollment). To enhance compliance, participants will be paid a $25 compliance bonus at each of the three EMA phases data is available for 16/24 hours of 80% of days within that phase.

| **Passive Parental Consent** | **Parental/student consent/assent** |  | **Cannabis users in CM discontinue cannabis use** |  |  |  |  |  |  |  |  |  |  |  |  |
| --- | --- | --- | --- | --- | --- | --- | --- | --- | --- | --- | --- | --- | --- | --- | --- |
|  | **V0** |  | **BL (V1)** | **V2** | **V3** | **V4** | **V5** | **V6** | **V7** | **V8** | **V9** | **V10** | **V11** | **V12** | **Exit interview** |
| Days since Baseline |  |  | 0 | 14 | 16 | 19 | 21 | 28 | 35 | 42 | 49 | 56 | 63 | 70 |  |
| Fitbit Inspire 3 |  |  | x | x | x | x | x | x | x | x | x | x | x | x |  |
| Phone Screener | x |  |  |  |  |  |  |  |  |  |  |  |  |  |  |
| EMA Assessments  (x indicates when EMA assessment phases begin) |  |  | x | x |  |  |  |  |  |  |  |  | x |  |  |
| *Substance Use Questionnaires* |  |  |  |  |  |  |  |  |  |  |  |  |  |  |  |
| AUDIT |  |  | x |  |  |  |  |  |  |  |  |  |  |  |  |
| CUDIT |  |  | x |  |  |  |  |  |  |  |  |  |  |  |  |
| CWS |  |  | x | x | x | x | x | x | x | x | x | x | x | x |  |

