**Potential Benefits to Society**

Information developed from this study may help researchers in the future. The expected scientific yield of the project is substantial. There is much to be learned from the project. Findings have the potential to have measurable implications on policy, prevention, and treatment efforts. The greatest benefit will be to future cohorts of adolescents who will benefit from what is learned from this research project.

The risks associated with this study are minimal and reasonable, particularly in light of the fact that significant knowledge will be gained.

1. **Statistical Analysis**

**Data preparation.** Six negative affect measures will be defined via composite averages and individual scores using EMA items: 1) the average over 5 items assessing depleted mood (scores for feeling Sad, Self-hatred, Numb, Hopeless, and Fatigued), 2) the average over 2 items assessing negative cognitive impacts (scores for feeling Disinterested and Inattentive), 3) the average over 3 items assessing negative activation (scores for feeling Agitated, Irritated, and Anxious), 4) the average over 3 items assessing passive suicidal ideation (scores for Thoughts about death, Wishing suffering could be over, and Better off as dead), 5) the individual item for suicidal urges, and 6) the individual item for non-suicidal self-injury urges. All items will be measured on a 0 (No, not at all) – 100 (Yes, very much) scale. Acute cannabis use will be defined as a binary indicator variable (1 = self-reported use in the hour preceding the current random prompt, 0 = no use in the last hour).Additionally, whether cannabis was used in the last hour to improve negative mood will be assessed on a 0 (No cannabis use) and 1 (No, not at all) – 100 (Yes, very much) scale.

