**Data analysis.**

**Aim 1: To test if negative mood and SI are temporarily relieved and stabilized through acute cannabis use (i.e., negative reinforcement cycle).** We will only use phase 1 data, the 2-week baseline period in which all participants may use cannabis. *Hypothesis 1.1:* We hypothesize that negative affect measures for a) the current random prompt, and b) the prior random prompt (a lag-1 term) will predict 1) greater cannabis use independent of motivating reason (i.e., lower probability for the zero component of the model), and 2) higher scores for motivated cannabis use to improve negative mood. Negative affect measures will therefore be converted to z-scores for this analysis and included as predictors for both the zero and non-zero components of the model. *Hypothesis 1.2:* We hypothesize that the binary indicator for cannabis use in the last hour will predict lower, less variable scores for the negative affect measures. Therefore, the binary use indicator will be included as a predictor for the beta regression residual variance term as well. *Hypothesis 1.3 (exploratory):* There will be within-subject correlates (e.g., concurrent other substance use, social context of use) and between-subject factors (e.g., cannabis use and depression severity, history of suicidal behavior) that moderate relationships between acute cannabis use and negative affect.

**Aim 2: To test if negative mood and SI initially increase with the start of abstinence and then decrease in both mean levels and variability after cannabis wash-out.** We will use phase 1 – 3 data, including predictors for a) group differences (CB-Abst vs. CB-Mon), b) differences by phase (phase 3 vs. phase 1 and phase 2 vs. phase 1), and c) terms for the group by phase interactions. All terms will be included as predictors for the beta regression residual variance term as well. We will only include data for the CB-Abst group with confirmed abstinence for phases 2 – 3. *Hypothesis 2.1:* We hypothesize that CB-Abst will show higher mean negative affect scores and greater variability during phase 2 compared to phase 1, while CB-Mon will show no differences between phases. *Hypothesis 2.2:* We hypothesize that CB-Abst will show lower mean negative affect scores and less variability during phase 3 compared to phase 1, while CB-Mon will show no differences between phases.

**Exploratory analyses:** To further assess heterogeneity in suicidal ideation, we will conduct a set of

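### Mood and suicidality are compared between arms only from EMA at baseline, week 1 and week 8, and only in confirmed abstainers; the PHQ-9 and C-SSRS collected at every visit have no stated as-randomised analysis

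*Protocol*

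**What the plan says.** - **Outcomes.** Protocol, Statistical Analysis, Data preparation: "Six negative affect measures will be defined via composite averages and individual scores using EMA items". The six are three mood composites, passive suicidal ideation, suicidal urges and self-injury urges.
- **Data for Aim 2.** Data analysis, Aim 2: "We will use phase 1 – 3 data, including predictors for a) group differences (CB-Abst vs. CB-Mon"), with phase and group-by-phase terms. CB-Abst data in phases 2 and 3 count only where abstinence is confirmed.
- **EMA timing.** Assessment Techniques: "Two 1-week EMA phases will occur during the randomized period (weeks 1 and 8 post randomization; Figure 1").
- **Withdrawal window.** General Description of Study Design justifies the 8-week period by "effects of withdrawal and residual cannabinoid exposure that generally subside in 4 weeks".
- **Second abstinence rule.** Under Protocol non-adherence, analyses that involve phase 1 and/or phase 2 admit only CB-Abst participants with two months of biochemically validated abstinence. If fewer than expected manage this, Helmert contrasts are formed, the first of which is called the intent-to-treat comparison.
- **Visit scales.** Assessment Techniques: "At V2-12, SI and behavior since last visit will be determined with the Columbia-Suicide Severity Rating Scale". The visit schedule places the C-SSRS and the PHQ-9 at every visit from V1 to V12.
- **Safety review.** Planned Safety Monitoring has the DSMB meet every 6 months to judge whether adverse events are more frequent in CB-Abst than in CB-Mon. It also has the principal investigator review other data bearing on safety differences, including clinical outcomes.

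**The concern.** The trial randomises depressed adolescents to stop cannabis, and hypothesis 2.1 predicts that mood and suicidal ideation first get worse. The planned outcome analysis sees the first week of that process and then nothing until week 8, although the Protocol expects withdrawal and residual exposure to last about four weeks.

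The selection rules add to the gap. A CB-Abst participant who deteriorates in week 3 and goes back to cannabis is not a confirmed abstainer in week 8. Under the two-month rule that participant's week-1 data can be dropped as well. The abstinence arm would then be represented by those who tolerated stopping. A modest rise in week 1 followed by a fall by week 8 among abstainers could be read as benefit after brief withdrawal, while worse courses in between were left out. Scales that could show those courses are collected in both arms, but no analysis of them is stated.

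**Working it through.** **1. The Protocol's own count.** Inputs: EMA of 14 + 7 + 7 days; 7-9 prompts per day, midpoint 8; Table 1 entries.
- Phase 1: 14 × 8 = 112, as in Table 1.
- Phases 1-3: 28 × 8 = 224, as in Table 1 (7 prompts would give 196, and 9 would give 252).
- Realistic scenario: 0.76 × 224 = 170.2, and 0.77 × 200 = 154, both as in Table 1.

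The power table thus counts the 28 EMA days and nothing from weeks 2-7.

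**2. Coverage.** From the visit schedule, V2 is day 14, V5 day 21, V8 day 42, V11 day 63 and V12 day 70.
- Randomised period: days 14-69, 56 days. EMA: days 14-20 and 63-69, 14 days, so 14/56 = 25%. Uncovered: 42 days (75%).
- Four-week window: days 14-41, 28 days. EMA: 7 days, so 7/28 = 25%. Uncovered: 21 days (75%).
- Visits that report on the uncovered 42 days: V6 to V11. Three of these, V6-V8, fall in the rest of the four-week window.

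**3. Who remains in the comparison.** Take a CB-Abst participant who is abstinent in week 1, worsens in week 3 and then resumes use.
- Under the Aim 2 rule, the week-8 data are excluded.
- Under the Protocol non-adherence rule as worded, any analysis that involves phase 1 or 2 requires two months of abstinence, so the week-1 data are excluded too. Aim 2 involves both phases.
- The as-randomised Helmert contrast is formed only if abstinence is lower than expected. No threshold is given, and no data source other than EMA is named.

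**4. Precision of an as-randomised PHQ-9 analysis.** Estimate: arm difference in the mean PHQ-9 over V5-V8 (days 21-42), adjusted for V2. Assumptions: equal SD at each visit; the same correlation ρ between any two visits, including V2; 154 completers split 77:77. The Protocol gives no value for ρ, so 0.3-0.7 is shown.
- Residual variance in SD² units: v = (1 + 3ρ)/4 − ρ²
- SE = √(v × 4/154)
- Detectable difference at 80% power, two-sided 5%: (1.96 + 0.84) × SE

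| ρ | v | SE (SD) | Detectable (SD) |
|---|---|---|---|
| 0.3 | 0.475 − 0.090 = 0.385 | 0.100 | 0.28 |
| 0.5 | 0.625 − 0.250 = 0.375 | 0.099 | 0.28 |
| 0.7 | 0.775 − 0.490 = 0.285 | 0.086 | 0.24 |

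**The case against.** The strongest reply is that safety in weeks 2-7 is monitored. Adverse events are scheduled at V2-V12, the DSMB compares them by arm, and the principal investigator reviews clinical outcomes. This stands. A reader might infer that worsening in weeks 2-7 is not reported at all, or that a suicide attempt would appear in no planned comparison. The Protocol does not support either: an attempt recorded as an adverse event would reach a between-arm review that is not limited to EMA weeks or to abstainers. What remains is narrower. The listed DSMB reports cover recruitment, retention and adverse-event descriptions, neither scale is named, and worsening that is not recorded as an adverse event has no stated by-arm summary.

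A second reply is that the statistical analysis plan is not at hand and may tabulate both scales, and that the Protocol sets the C-SSRS alongside a primary EMA measure. This also stands, so one cannot conclude that the scales will go unanalysed. But the Protocol is not merely silent. It fixes the outcomes, phases and exclusions for Aim 2, and the abstainer-only rules are its own text.

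A third reply is that hypothesis 2.1 concerns only the first week of withdrawal, and that the four-week remark justifies the study length without saying when harm is expected. Both are correct. No limit on hypothesis 2.1 is needed, and the 28 days are used here only as the Protocol's own statement of how long these effects may last.

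Finally, the Helmert contrast does offer an intent-to-treat comparison, but only conditionally.

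**Conclusion.** The point holds as a gap in the planned between-arm analysis, not as an absence of safety monitoring. EMA covers 25% of the randomised period and 25% of the Protocol's withdrawal and residual-exposure window. These figures come from the schedule and need no assumption. The abstinence rules can remove those who worsen and resume use, possibly at week 1 as well as week 8, and the only as-randomised contrast depends on an undefined shortfall in abstinence. The PHQ-9 and C-SSRS in both arms could fill the gap, but no by-arm analysis of them is stated.

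A reader might go further and infer that the trial would miss a real harm in weeks 2-4. The documents give no size or shape for such an effect. If one assumes a difference in those weeks and none in weeks 1 and 8, the EMA analysis misses it by construction, so that is no evidence of its likelihood. The precision figures rest on the assumed correlation of 0.3-0.7, equal variances and 154 completers.

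**What to change.** Add to Data analysis, Aim 2, a supportive safety analysis by arm as randomised, regardless of abstinence:

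1. **PHQ-9** total at V3-V12 in a repeated-measures model adjusted for V2 PHQ-9, with the arm difference averaged over V5-V8 named as the withdrawal-window estimate.
2. **C-SSRS** over V3-V12: the number and proportion per arm with any suicidal behaviour, and the worst ideation level, each with a 95% confidence interval for the arm difference. Use V2 as baseline, because it shares the since-last-visit recall of the later visits, whereas V1 asks about the past month.
3. Include both in the reports to the DSMB.

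This stands beside the abstainer analysis and does not depend on which abstinence rule is applied there. It does require visit data after resumed use; the Protocol's Helmert group of CB-Abst participants who do not abstain implies that these are kept.

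The cost is two extra analyses of data already scheduled, with no added visits or measures. The C-SSRS intervals will be wide, so that part supports estimation and not a firm test.

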**Treatment Assignment and/or Randomization**

If participants meet eligibility criteria and a signed consent form has been received from a parent/guardian, they may be contacted and scheduled for a baseline session. For participants aged 18 years, baseline sessions may be scheduled prior to obtaining consent (as consent will be obtained at baseline prior to administering any study procedures). For all participants, a member of the study team will discuss the consent/assent form with the participant, provide answers to any questions, and, if the participant is interested, a licensed clinician will obtain informed consent/assent. The participant will then be given a signed copy of the consent/assent form.

Once enrolled and after the baseline phase (EMA Phase 1; Baseline as Usual), participants will be scheduled for randomization, which will employ a 2-arm, within-subject, parallel group design to examine effects of short- and longer-term withdrawal across 8 weeks of cannabis abstinence on depression and SI. Participants will be randomized to 8 weeks of abstinence with contingency management (CB-Abst: n=100) or non-contingent monitoring with no abstinence requirement (CB-Mon: n=100) using a 1:1 ratio in blocks of 6. A subset of study staff who will administer surveys and questionnaires querying about mood and suicidality will be blind to group assignment. Randomization will be based on a computerized scheme developed by the study statistician. Randomization will be stratified by age (<=14 years old vs >=15 years old), sex (male vs female), and depression severity (mild/moderate vs. Moderately severe/severe). A key aspect of the approach is that the 8-week period is long enough to observe true changes due to cannabis discontinuation, separate from effects of cannabis withdrawal and residual cannabinoid exposure. Groups will complete 1-week of EMA in weeks 1 (EMA Phase 2; Randomized Withdrawal) and 8 (EMA Phase 3; Randomized Sustained Abstinence) of the randomized study period.

Individuals randomized to monitoring who incidentally stop using cannabis, or express an interest in discontinuing cannabis, will not be removed from the study. If desired, these individuals will be provided with substance use resources at the time of interest in cessation.

1. **STUDY PROCEDURES**

Study procedures are nearly identical to those used in IRB approved pilot protocol (#2021P002416).

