**Statistical models.** Separate analyses will be conducted for each negative affect measure. Statistical models will assume that a) data are a mixture of a non-zero continuous component and zeros, and b) the continuous component will follow a beta distribution (i.e., scores will be scaled to be between 0 and 1). Models will include 1) a participant-varying lag-1 autocorrelation term (to handle repeated measures) and 2) a participant-varying probability term governing the occurrence of zeros (to allow for individual differences). Additional covariates will include weekday (categorical, Monday-Sunday), time of day (categorical, 6:00-11:00, 11:00-16:00, 16:00-21:00), age (continuous), and gender (categorical). To test specific hypotheses, additional predictors will be included as needed for a) the beta regression, b) the residual variance term of the beta regression, and c) the probability term governing zeros.

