**Protocol non-adherence.** Analyses involving phase 1 and/or phase 2 of EMA data collection, will only consider CB-Abst participants who have biochemically-validated CB abstinence for two months because the goal is to study the effect of abstinence on change in mood and SI. If fewer than expected CB-Abst abstain from CB use for the full two months, we will form Helmert contrasts: those in CB-Mon (a), CB-Abst who do not abstain (b), and CB-Abst who abstain (c). The 1^st^ Helmert contrast will compare a to b+c and will be the intent to treat comparison. The 2^nd^ contrast will compare b to c, which corresponds to the post hoc sensitivity analysis of interest. Similar considerations will be made if participants in CB-Mon incidentally discontinue CB use during the study.

**Power analysis and justification of recruitment targets for the confirmatory cohort.** The R package ‘EMAtools’ (version 0.1.3; Kleiman, 2017) was used to determine the power for the proposed analyses. Preliminary analyses from the exploratory study found effect size estimates for significant effects ranged from 0.19 to 0.44, and that 77% of participants completed all phases of the study, completing on average 76% of all prompts. Estimates of the power were therefore computed to detect a weak effect (a Cohen’s d of .2) based on linear multi-level models using the nesting structure for the proposed EMA analyses and an intra-class correlation of .09. Table 1 shows the breakdown of estimates power based on the hypothesis being tested under two scenarios: 1) an ideal scenario with the full proposed number of participants and responses, and 2) a realistic scenario where 77% of participants complete 76% of entries.

Table 1: Power estimates by hypothesis and attrition scenario (ideal versus worse-case)

| Hypothesis | N (%) for sample size | N (%) of completed entries | Power |
| --- | --- | --- | --- |
| 1.1 - 1.2 | 200 (100%) | 112 (100%) | 99% |
|  | 154 (77%) | 85 (76%) | 93% |
| 2.1 - 2.2 | 200 (100%) | 224 (100%) | 99% |
|  | 154 (77%) | 170 (76%) | 94% |

1. **Monitoring and Quality Assurance**

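### In the intent-to-treat version of the Aim 2 comparison, a free arm difference at pre-randomisation phase 1 costs some precision; adjust that contrast for phase 1

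*Protocol*

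**What the plan says.** Protocol, Statistical Analysis, Data analysis, Aim 2: the model uses phases 1 to 3, "including predictors for a) group differences (CB-Abst vs. CB-Mon), b) differences by phase" (coded "phase 3 vs. phase 1 and phase 2 vs. phase 1") and "terms for the group by phase interactions". The same terms enter the residual-variance part of the beta regression.

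Protocol, Treatment Assignment and/or Randomization: "Once enrolled and after the baseline phase (EMA Phase 1; Baseline as Usual), participants will be scheduled for randomization". Phase 1 is therefore a pre-randomisation measurement.

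Protocol, Statistical Analysis, Statistical models: "Additional covariates will include weekday (categorical, Monday-Sunday), time of day", age and gender. No phase-1 outcome value is listed, and no common baseline level is imposed on the arms.

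Two analysis sets are in play. The Aim 2 paragraph restricts the abstinence arm: "We will only include data for the CB-Abst group with confirmed abstinence for phases" 2 and 3. The Protocol non-adherence paragraph adds a comparison of everyone randomised, to be used if fewer CB-Abst participants than expected abstain for the full two months. With CB-Mon as a and the CB-Abst non-abstainers and abstainers as b and c, the first "Helmert contrast will compare a to b+c and will be the intent to treat comparison". That paragraph gives the group coding but does not say how phase 1 enters the model.

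**The concern.** With phase 1 as the reference phase, the group main effect is the phase-1 arm difference. Among all randomised participants that difference is zero in expectation, because nothing has yet been assigned. Estimating it freely ignores this knowledge and makes each group-by-phase term a difference in phase changes, taken on the model's link scale.

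Such a contrast subtracts the whole observed phase-1 difference, whereas the best prediction of a later difference uses only part of it. Two things follow: the variance is at least as large as with baseline adjustment, and a chance phase-1 imbalance is over-corrected, which moves the estimate in the opposite direction. At stake is the precision of the one Aim 2 comparison that randomisation fully protects, in a trial that plans for 154 of 200 participants completing.

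**Working it through.** **Inputs.** ICC 0.09, effect d = 0.2, 154 of 200 participants and 76% of entries (Protocol, Power analysis). The table's 112 entries for phase 1 and 224 in total leave 56 each for phases 2 and 3. At 76% these become about 85 and 43. The arms are taken as equal, 154 / 2 = 77 each. Two-sided alpha of 0.05 is assumed, since the protocol states none.

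**The protocol's own power figures.** Effective N = participants × entries / [1 + (k − 1) × 0.09], split into two equal groups.
- Hypotheses 2.1–2.2, full: 200 × 224 / (1 + 223 × 0.09) = 44,800 / 21.07 = 2,126; power 99.6% (stated 99%).
- Hypotheses 2.1–2.2, attrition: 154 × 170 / 21.07 = 1,243; power 94.1% (stated 94%).
- Hypotheses 1.1–1.2: 99.5% and 93.2% (stated 99% and 93%).

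The attrition rows reproduce only with k kept at the full entry count (224 or 112). These figures are for a simple two-group mean difference. They do not bear on how phase 1 is handled, so that needs its own calculation.

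**Formulas (linear approximation, person-by-phase means, total variance 1).** Let v1 and v2 be the variances of a participant's phase-1 and later-phase means, and c their covariance.
- Free phase-1 difference: v1 + v2 − 2c
- Baseline-adjusted or constrained: v2 − c²/v1
- Share of a chance phase-1 difference over-corrected: 1 − c/v1

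**Base case: stable person means, independent prompts.**
- v1 = 0.09 + 0.91/85 = 0.1007; v2 = 0.09 + 0.91/43 = 0.1112; c = 0.09; correlation 0.85
- Free: 0.1007 + 0.1112 − 0.18 = 0.0319
- Adjusted: 0.1112 − 0.0081/0.1007 = 0.0307
- Variance ratio 1.04; loss 1 − 0.0307/0.0319, which is 3.6% before rounding, or about 5.5 of 154 participants
- Over-correction: 1 − 0.09/0.1007 = 11%

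**Other cases.** The protocol models lag-1 autocorrelation but gives no value. For an assumed value r, the prompt-level terms are multiplied by (1 + r)/(1 − r), that is 1.86 at r = 0.3 and 3 at r = 0.5. The protocol also gives no figure for how far person means shift between phases. An assumed phase-specific share of the between-person variance reduces c to 0.09 × (1 − share).

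| Case | Variance ratio | Loss of N | Over-correction |
|---|---|---|---|
| Stable means, independent prompts | 1.04 | 4% | 11% |
| Stable means, r = 0.3 (assumed) | 1.06 | 6% | 18% |
| Stable means, r = 0.5 (assumed) | 1.10 | 9% | 26% |
| 25% phase-specific (assumed), independent prompts | 1.17 | 14% | 33% |
| 50% phase-specific (assumed), independent prompts | 1.34 | 25% | 55% |

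In the last row, power at d = 0.2 with 77 per arm is 94.5% for the free contrast and 98.4% for the adjusted one.

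**Scale of the over-correction.** The standard error of a chance phase-1 difference is √(2 × 0.1007/77) = 0.051 SD. An imbalance of that size shifts the contrast by 0.11 × 0.051 = 0.006 SD in the base case and 0.55 × 0.051 = 0.028 SD in the last row, against a target effect of 0.2 SD.

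**Simulation check.** 77 per arm, no true effect, 10,000 trials for each of the first and last rows. Variance ratios were 1.03 and 1.34. The free contrast averaged about zero. Its slope on the chance phase-1 difference was −0.10 and −0.56, against about zero after adjustment.

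**The case against.** The strongest objection is that the Aim 2 paragraph describes a confirmed-abstainer analysis, for which a free group term is right. Participants who abstain may differ systematically at phase 1 from CB-Mon, so forcing a common baseline there could introduce bias. This stands. A reader might infer that the main Aim 2 model is mis-specified; the documents do not support that, and the point is confined to the all-randomised contrast.

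That contrast is a conditional fallback, and the protocol does not spell out its model. This also stands. The point assumes that the Aim 2 terms carry over, which is the natural reading because no other model is given. Hypotheses 2.1 and 2.2 are moreover worded as phase changes within each arm, so the arm contrast tests them only indirectly.

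A reader might also infer a large loss from the equal-variance rule, under which the loss is (1 − ρ)/2: 35% at a between-phase correlation of 0.3 and 25% at 0.5. The protocol gives no such correlation. Its ICC and entry counts imply about 0.85 when person means are stable, hence the figure of about 4%. That is the favourable end, since it assumes independent prompts while the protocol itself models autocorrelation. Anything much larger depends on assumed shifts between phases.

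Finally, group, phase and group-by-phase is a standard specification, and stratifying on depression severity limits imbalance in a related variable. Both are true. Stratification on a two-level category does not remove imbalance in six separate EMA outcomes.

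**Conclusion.** The point holds for the intent-to-treat Helmert contrast only, and as a minor matter of efficiency. If the Aim 2 terms are carried over, the contrast is less precise than it need be by about 4% of N on the protocol's ICC with stable person means and independent prompts. The loss is 6% to 9% with an assumed lag-1 autocorrelation of 0.3 to 0.5, and about 25% if half the between-person variance is assumed phase-specific. Over-correction of a chance phase-1 imbalance runs from 11% to 55% across these cases.

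It would be wrong to conclude that the analysis is invalid or biased: over randomisations the free contrast is centred on the true effect. All figures come from a linear approximation on person-by-phase means. The planned model is a beta regression with a zero component and a lag-1 term, so the sizes are indicative.

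**What to change.** For the all-randomised contrast only, specify one of two forms:
- model phases 2 and 3 with each participant's phase-1 mean as a covariate; or
- keep phases 1 to 3 and constrain the arms to a common phase-1 level in every model component that carries a group term (mean, residual variance and, if used, zero probability).

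Leave the free group term in the confirmed-abstainer analysis, and state that selection after randomisation is the reason. Phase-1 adjustment could be added there too, but it would not cure that selection.

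The cost is somewhat more model specification. It needs no new data and adds no burden for participants.
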